Due to symptoms having a clinical similarity to posttraumatic stress disorder, it is suspected that interventions based on therapeutic approach for PTSD can be equally effective for secondary traumatic stress [22]. In national and international guidelines, exposition therapy approaches as first line treatment for posttraumatic stress disorder are recommended [23–27]. Among others, eye movement desensitization and reprocessing (EMDR) is a validated and effective treatment for PTSD [28]. While the underlying effect of bilateral eye stimulation is not fully understood [29], there is large evidence of EMDR effectively reducing symptoms of traumatic stress [30]. The planned study will examine the effectiveness of EMDR on secondary traumatic stress symptoms in a sample of interpreters working in refugee care. Therefore, a quasi-randomized controlled trial will be conducted, with a waitlist-control group to compare the development of symptoms of secondary traumatic stress in each group with and without EMDR intervention. The aim is to examine the hypothesis that EMDR intervention significantly reduces symptom burden of secondary traumatization compared to waitlist control.

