### Randomization

Participants will be randomly assigned in either the intervention group or waiting list control group. Because of a rather small sample size, and to ensure seamless and reliable allocation for available therapists, this will be carried out through alternating allocation of participants at the initial screening interview for the study to avoid large differences in sample size. The allocation to one of the two groups is therefore already determined before inclusion in the study. Participants will be informed verbally at the time of the initial screening interview by the responsible therapist. Blinding is neither possible for the participant (as filling out of questionnaires during waiting time), nor for the EMDR therapist, as collaborative planning is necessary for the distribution of participants, as the therapists mainly work clinically. The team of EMDR therapists available to conduct the intervention comprises of five persons. Both groups will receive the same intervention that is planned as follows. A detailed participant timeline can be found in Fig. 2.

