### Concomitant care, serious adverse events

Due to ethical considerations, participants can receive psychotherapeutic treatment or psychopharmacological medication during the study. The existence of simultaneous psychotherapy or psychopharmacological medication will be surveyed in every data collection point so that any changes in this regard are recorded. By conducting the study, no serious adverse events (SAE) are expected. Cases will be supervised regularly by an external EMDR supervisor. However, if in any case of a serious adverse event happens, this will be immediately and directly reported contact to the study team and the principal investigator. Serious adverse events include suicidal ideation, severe self-harm, or severe and ongoing exacerbation of the symptoms of secondary traumatization in the context of EMDR treatment. These will be reported systematically in non-standardized language as well as discontinuation of the study participations for other reasons. Responsible therapists will be informed about this procedure prior to the study. It will be reported by Serious Adverse Event Report Form [54]. Handling of adverse events will be decided individually. Therapeutic treatment through the outpatient clinic of the department is possible if required. A short-term increase in psychological stress is inherent in the EMDR procedure, as it is a trauma confrontation procedure. This normally subsides within a few days. This is not systematically reported as harm, as it could arise as part of the treatment, but will be discussed in the joint sessions with the responsible therapist.

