### Statistical analyses

The quantitative data will be monitored and analyzed by the study team and colleagues of the research group using SPSS [55]. As the statistical evaluations are carried out by the study team with the support of the biostatistician, blinding is not performed. Baseline characteristics will be compared to assessed differences of the intervention and control group, especially regarding the symptom load of secondary traumatization symptoms as well as on the presence of self-experienced traumatic events and PTSD symptoms. The effectiveness of the EMDR intervention will be assessed using a piece wise growth curve model [56], a type of the latent growth curve model, based on the assumption that change of symptomatology along the study duration is not linear but depends to certain change points. In this model, growth rates between different time periods are compared. The main criterion of interest is the symptom load of secondary traumatic stress assessed with the FST. Further parameters to be analyzed are symptom load of depression, anxiety, and somatic distress as well as professional quality of life and quality of life. For the data collected, time periods of interest are before and after the intervention for intervention group (T1–T2) and waitlist control group (T2–T3), after the intervention to follow up for both groups (intervention group T2–T3/T4, control group T3–T4), and before and after the waiting period for the control group (T1–T2). Covariates will include current psychiatric treatment, current psychopharmacological prescription or medication change, and personal traumatic experience. The data of all randomized participants who filled out the pre-and post-questionnaires and, from the intervention group, who completed at least two sessions (one preparatory session with investigation of the experiences that will be processed (phases 1–2) and at least one confrontational session (phase 3–7/8) will be included in the analysis (per-protocol analysis). Reasons for incomplete participation in the intervention will be presented descriptively. With regard to the calculation of the sample size for a piece wise growth model, there is only scarce literature on how to do so [57]. Therefore, the sample size is calculated on the basis of analysis of variance (ANOVA) with repeated measures. According to literature, EMDR shows large effect sizes (*g* = 1.01 (CI 95% 0.42 to 1.62). For the present study, however, the effect size of EMDR on secondary traumatization is not known yet. Therefore, a conservative calculation with a medium effect (*d* = 0.5) was carried out. Assuming a type I error of *α *= 0.05 and a statistical power of 0.8, a sample size of *n *= 34 is calculated [58]. Assuming a drop-out rate of 18% [59], a sample size of 40 is aimed for. Missing data will be first identified and analyzed. No further measures will be carried out in case of missing data < 5%. If > 5% of the data are missing, it will be examined whether these are related to certain variables, such for example with symptom burden and whether patterns can be recognized. If these data are missing at random, no further procedures will be carried out. If missing values are systematically related to one of the recorded variables, a multiple imputation can be performed [60]. Due to a lack existing studies, the distribution of the data cannot be estimated. Therefore, the collected data is first checked for normal distribution and if not normally distributed transformed in order to carry out the analyses with transformed data.

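### Treatment covariates that include changes after allocation can move the estimate away from the total effect of EMDR versus waiting

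*Protocol article*

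**What the plan says.** The Statistical analyses section assesses effectiveness with a piecewise growth curve model of the FST over T1 to T4 and fixes the covariates: "Covariates will include current psychiatric treatment, current psychopharmacological prescription or medication change, and personal traumatic experience". It gives no time point for current treatment or prescription. It does not name an unadjusted primary estimate, nor does it call the adjusted model a sensitivity analysis.

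The section on concomitant care states that "participants can receive psychotherapeutic treatment or psychopharmacological medication during the study". This information "will be surveyed in every data collection point so that any changes in this regard are recorded". The same section adds: "Therapeutic treatment through the outpatient clinic of the department is possible if required".

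On timing, the Randomization section says: "The allocation to one of the two groups is therefore already determined before inclusion in the study". It continues: "Participants will be informed verbally at the time of the initial screening interview by the responsible therapist". Participants are not blinded.

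The Background section gives the hypothesis to be tested, that "EMDR intervention significantly reduces symptom burden of secondary traumatization compared to waitlist control".

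**The concern.** Adjusting for a characteristic fixed before allocation leaves the target of the comparison alone and may sharpen it. Adjusting for something that happens after allocation is different if the allocation can influence it.

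Here it can. A participant who knows that treatment is about six weeks off may look for help elsewhere, and one who improves under EMDR may stop other care. Outside care is unrestricted, and outpatient treatment in the department is available. Starting or changing treatment is also a sign of how the symptoms are developing. Two distortions follow:

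- **Mediation.** If outside treatment works and is used unequally, adjustment removes that part of the difference between the groups.
- **Selection.** If worsening symptoms prompt the change, then comparing people with the same change status compares people of different underlying severity in the two groups.

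The hypothesis concerns EMDR compared with waiting, whatever other care follows from being in either group. What is at stake is whether the primary estimate answers that question.

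**Working it through.** **Timing of each covariate**

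- Personal traumatic experience: essentially history before allocation. No objection.
- Current psychiatric treatment and current prescription: surveyed at T1 to T4. The T1 value is a baseline value; values at T2 to T4 come after allocation.
- Medication change: the concomitant-care section says the repeated survey exists to record changes, so the natural reading is change during the study, after allocation.

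**The plan's own figure**

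The only related figure is the sample size. Inputs from the article: d = 0.5 (f = d/2 = 0.25), alpha 0.05, power 0.8, repeated-measures ANOVA. Assumed: two groups, m = 2 measurements, correlation rho = 0.5.

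lambda = f² × N × m/(1 − rho) = 0.0625 × 34 × 2/0.5 = 8.5, which gives power 0.807. The stated 34 reproduces. The formula has no covariate term, so changing the covariates leaves 34, and the target of 40, as they are.

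**Size of the mediation shift**

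The article gives no uptake rates and no effect of other treatment, so both are assumed. If a fraction p0 of the waitlist and p1 of the EMDR group take up other treatment worth b SD, adjusted and unadjusted effects differ by

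shift = (p0 − p1) × b

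| Difference in uptake | b = 0.25 SD | b = 0.50 SD | b = 0.75 SD |
|---|---|---|---|
| 0 | 0 | 0 | 0 |
| 0.05 (e.g. 10% vs 5%) | 0.0125 | 0.025 | 0.0375 |
| 0.20 (e.g. 25% vs 5%) | 0.05 | 0.10 | 0.15 |

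The range is about 0.01 to 0.15 SD. Relative to d = 0.5 this is 0.0125/0.5 = 2.5% to 0.15/0.5 = 30%.

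**Direction**

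A large-sample simulation (1,000,000 people per scenario) added selection by severity. All inputs are assumed: direct EMDR effect −0.50 SD, severity weight 0.7 on the outcome, residual variance 0.51. Where uptake depends on severity, its log-odds rise by 0.8 per SD, and the rates below apply at average severity.

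| Uptake, waitlist vs EMDR | Effect of other treatment | Driven by severity | Unadjusted | Adjusted |
|---|---|---|---|---|
| 30% vs 30% | −0.5 | yes | −0.503 | −0.503 |
| 30% vs 10% | −0.5 | no | −0.398 | −0.497 |
| 30% vs 10% | none | yes | −0.501 | −0.400 |
| 30% vs 10% | −0.5 | yes | −0.399 | −0.398 |
| 20% vs 30% | none | yes | −0.499 | −0.547 |

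The unadjusted figure is the total effect of EMDR versus waiting. With equal uptake there is no shift. In row two adjustment makes EMDR look better than the total effect, and in row three worse. In row four the two distortions cancel. Over all scenarios run, the shift lay between about −0.10 and +0.10 SD.

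**The case against.** **Current may simply mean current at T1.** T1 is one of the survey points, and T1 status would be largely unobjectionable. A medication change could even mean a recent change before entry. A reader might infer that every treatment covariate is certainly measured after allocation; the article does not support that. What stands is narrower: medication change, read with the stated reason for repeated surveying, points to changes during the study, and the date of the other two is left open.

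**The analysis plan may settle it.** It may. But the article itself fixes the covariate set and includes an item that is not naturally a baseline value, so this is a stated choice and not merely an absent detail.

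**Adjustment isolates EMDR from other therapy.** A reader might infer that the adjusted estimate has no causal meaning. That goes too far. An effect with other treatment held equal can be interpreted, as row two of the simulation shows, where adjustment recovers the direct effect. But it answers a different question from the stated hypothesis, and it requires that no unmeasured factor drives both treatment uptake and the FST. Evolving severity is an obvious candidate.

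**The shift may be small.** This is fair. The first interval is about six weeks, and waitlist participants know they will receive the same intervention. With about 33 analysed (40 × 0.82 = 32.8), the standard error of a simple two-group difference is about 2/√33 = 0.35 SD, well above any shift shown here. The per-protocol restriction and alternating allocation also separate the estimate from the effect of allocation; those are separate matters.

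**Conclusion.** The concern holds for medication change, and for current treatment and prescription if values after T1 are used. Adjusting for them can move the primary estimate away from the total effect of EMDR versus waiting, and the direction cannot be known in advance. The size is also unknown: about 0.01 to 0.15 SD under the assumed uptake differences and treatment effects, and nil if allocation does not affect treatment use. A reader should not infer that a material bias has been shown, because the article contains no uptake rates.

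Nor should a reader infer a fault from the absence of the T1 FST among the covariates. In a growth model covering T1 to T4, the T1 FST is already the first outcome measurement and needs no separate term.

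The point deserves correction because the remedy is simple and because the analysts are not blinded, so the choice of covariate date should not be left until the data are seen.

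**What to change.** In the Statistical analyses section, replace the covariate sentence with one stating that:

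- the primary model adjusts only for T1 values: psychotherapy or psychiatric treatment (yes/no), psychopharmacological medication (yes/no) and personal traumatic experience;
- medication change and any other treatment after T1 are left out of the primary model and tabulated by group and time point;
- a model that includes them is reported only as a labelled sensitivity analysis, described as addressing the effect with other treatment held equal.

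Because participants learn their group at the screening interview, T1 treatment status should be defined as what was already in place at that interview.

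The cost is a short change of text. The survey already covers treatment at every data collection point, so no item is added, and the sample size stays as it is.

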#### Quality of life

Beyond the previous aspects, health-related quality of life (Short Form 12, SF-12 [48]) as well as psychological wellbeing (WHO-5 [37]) will be examined. The SF-12 questionnaire is a non-disease-specific instrument and covers 8 categories, which include questions about limitations in physical or social activities, hindrance of usual role activities due to physical or psychological problems, physical pain, general mental health, vitality, and general health perception. Two scales are used to measure physical (Physical Component Summary, PCS)) and psychological aspects (Mental Component Summary, MCS)) of health-related quality of life, which show a good internal consistency with Cronbach’s *α* = 0.89 (PCS) and *α* = 0.89 (MCS) [49, 50]. Summary scores for each scale are calculated, with an average ≥ 50 indicating a better mental or physical health than the average population and ≤ 50 indicating a worse mental or physical health than the average population. The WHO-5 is one of the most frequently used questionnaires to measure general, subjective well-being with a good internal consistency (Cronbach’s *α* = 0.80–0.92). Psychological well-being is recorded using five questions about a good mood, inner peace and relaxation, energy, ability to regenerate through sleep, and enthusiasm in the last 2 weeks. These can be agreed on a scale of 1–5 with 0 = at no time and 5 = all the time. A total score is calculated based on the number of points and multiplied by 4, with a score of 0 representing the worst and a score of 100 representing the best well-being. Used as a screening tool for depression, a sum score ≤ 50 indicates a positive screening result [37]. For the analysis of the results, the changes in the total scores or the described subscales of the primary and secondary outcomes before the intervention (T1) compared to after the intervention (T2, T3), as well as in the comparison of the intervention group with the control group, are of interest.

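### The plan does not say how T1 FST enters the primary group contrast; with group-specific intercepts it is a change-score comparison, less precise than one conditional on T1

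*Protocol article*

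**What the plan says.** The model is named in Statistical analyses: "The effectiveness of the EMDR intervention will be assessed using a piece wise growth curve model [56], a type of the latent growth curve model". The quantity compared is a rate of change: "In this model, growth rates between different time periods are compared". The outcome is clear: "The main criterion of interest is the symptom load of secondary traumatic stress assessed with the FST".

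The covariate list is explicit: "Covariates will include current psychiatric treatment, current psychopharmacological prescription or medication change, and personal traumatic experience". T1 FST is not on it. The same section foresees that the groups may differ at the start: "Baseline characteristics will be compared to assessed differences of the intervention and control group, especially regarding the symptom load of secondary traumatization symptoms". It does not say what a difference would change in the model.

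The closing lines of the Quality of life section say that what matters is change in scores "before the intervention (T1) compared to after the intervention (T2, T3), as well as in the comparison of the intervention group with the control group".

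The sample size in Statistical analyses rests on repeated-measures ANOVA with a medium effect, alpha 0.05 and power 0.8. It gives 34, raised to 40 for 18% drop-out. Under Randomization, "this will be carried out through alternating allocation of participants at the initial screening interview", and the arm is settled before inclusion. Under Participants and recruitment, entry requires an FST score of at least 65, so every participant has a T1 value.

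The article does not state whether the intercept is common to the groups or group-specific, or whether the slope depends on the starting level.

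**The concern.** The T1 score is usually among the strongest predictors of the T2 score on the same scale. A group contrast in T1-T2 growth rates with a separate intercept per group subtracts T1 with a coefficient of exactly 1. The regression of T2 on T1 normally has a slope below 1, so the subtraction over-corrects any T1 difference and adds variance. The listed covariates do not replace T1 FST.

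Precision matters here. About 33 people are expected to be analysed (40 x 0.82 = 32.8), and the Discussion itself names too few participants as a possible limitation. If the parameterisation is chosen after the baseline comparison has been seen, the estimate will depend on that choice.

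**Working it through.** **1. The plan's own figure.** For a repeated-measures ANOVA with two groups and m = 2 time points, reading the medium effect as f = 0.25 and assuming correlation rho = 0.5, the noncentrality is N m f²/(1 - rho) = 34 x 2 x 0.0625/0.5 = 8.5 on 1 and 32 df. Power is 0.807, and 34 is the smallest even N that reaches 0.80. The figure reproduces as the two-time-point group-by-time interaction, which is the change-score test. The within-person time effect in the same layout gives the same 34. Three or four time points give 28 and 24; the between-group factor gives 98, 86 and 82 for m = 2, 3 and 4. The sample-size basis therefore fits a change-score contrast but does not prove that one is planned.

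**2. What the growth model estimates.** In one simulated data set of 34 people with two time points:

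| Specification | Estimate | Model SE |
|---|---|---|
| Growth model, group-specific intercepts | -1.103 | 0.399 |
| Difference in change scores | -1.103 | |
| Growth model, common intercept | -0.811 | 0.346 |
| ANCOVA on T1 | -0.809 | |

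The intercept specification decides which of two estimators is used.

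**3. Size of the loss.** Take the unselected FST standard deviation as 1, rho as the T1-T2 correlation before selection, and k² as the T1 variance in the enrolled sample. Per person:

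- change score: k²(1 - rho)² + (1 - rho²)
- conditional on T1, slope known: 1 - rho²
- share of the change-score variance removed: k²(1 - rho)² / [k²(1 - rho)² + 1 - rho²]

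For strong range restriction, assume that the 21% prevalence cited in the Background is the share above the entry cut-off and that FST is normal. Then z = 0.8064, the density is 0.2882, the ratio is 0.2882/0.21 = 1.3724, and k² = 1 + 1.1067 - 1.8835 = 0.223.

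| T1 variance k² | rho = 0.3 | rho = 0.5 | rho = 0.7 |
|---|---|---|---|
| 0.223 | 0.109/1.019 = 10.7% | 0.056/0.806 = 6.9% | 0.020/0.530 = 3.8% |
| 0.5 | 0.245/1.155 = 21.2% | 0.125/0.875 = 14.3% | 0.045/0.555 = 8.1% |
| 1.0 | 0.49/1.40 = 35% | 0.25/1.00 = 25% | 0.09/0.60 = 15% |

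In the last row the conditional variance is (1 + rho)/2 of the change-score variance. At rho = 0.5, for the effect that n = 34 implies under step 1 (a 1.0 SD difference in change), power at N = 34 goes from 0.807 to 0.903.

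**4. Bias, and the price of estimating the slope.** In 20,000 simulated trials (N = 34, rho = 0.5, unrestricted T1, true effect -1.0), both estimators average -0.999. The SD is 0.341 for change and 0.301 for ANCOVA. A T1 imbalance enters the change estimate with coefficient about -0.49 (theory -(1 - rho) = -0.50) and the ANCOVA estimate with about 0. With the slope known instead of estimated the SD is 0.2958, so estimating it costs 0.3008²/0.2958² = 1.034, about 3% of variance.

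**5. Imbalance is not a second harm.** With 16 per arm and k² = 0.223, the T1 group difference has SD sqrt(0.223 x 2/16) = 0.167. At rho = 0.3 it shifts the change contrast by 0.167 x 0.7 = 0.117. Squared, that is 0.0137. The whole variance of the contrast is 1.019 x 2/16 = 0.127, and 0.0137/0.127 = 10.7%, the same figure as in the table.

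**The case against.** A reader might infer from the covariate list that the plan prescribes a raw change-score test that chance imbalance will bias. The article does not support that. In a growth model T1 is the first response, so its absence from the covariates is normal. The intercept is not specified, and a common intercept or a slope that depends on starting level would already adjust. Other covariates are included, so the contrast is not raw. Over chance imbalance there is no bias, and the usual standard error already carries the variation.

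The equivalence with change scores also has limits. It holds for the T1-T2 contrast with free group intercepts. A model that forces one treatment-phase slope on the intervention group's T1-T2 and the waitlist group's T2-T3 would not reduce to it.

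The strongest point concerns allocation. Alternation is predictable, so T1 differences need not be chance. If the arms differ stably for reasons other than the T1 score, subtraction removes that difference, whereas conditioning may not, and a common intercept assumes it away. Group-specific intercepts are therefore defensible.

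Finally, the gain may be small, and it depends on a correlation and a degree of range restriction that the protocol does not give.

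All of this stands as a limit on the claim. What remains is that the article fixes a covariate list, speaks of change from T1, plans a baseline comparison without a consequence, and leaves open a choice that alters the estimate.

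**Conclusion.** The point holds as a conditional one. With group-specific intercepts, the T1-T2 contrast is a change-score comparison apart from the listed covariates. The avoidable variance is about 4-11% under strong range restriction (roughly 2-6% of the standard error) and 15-35% without it (roughly 8-19%). Both ranges assume rho from 0.7 to 0.3; the first also assumes normality and the 21% reading.

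These figures take the slope as known. Carrying over the roughly 3% cost of estimating it, the gain at the low end almost vanishes (0.962 x 1.034 = 0.995), while at the high end most of it remains (0.65 x 1.034 = 0.672). The case for the change therefore rests on having one stated, baseline-adjusted contrast, with a precision gain between negligible and about a third of the variance. The shift from an observed T1 imbalance is this same loss seen in one trial and should not be counted again.

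**What to change.** State in the analysis section that the primary contrast is the group difference in FST at T2 conditional on T1 FST. Either ANCOVA or the growth model with the T1-T2 slope regressed on T1 level will do. Regressing observed change on observed T1 gives the same group coefficient as regressing T2 on T1. Keep the listed covariates, and treat each secondary scale in the same way with its own T1 value. Say that the baseline comparison is descriptive and does not decide the model.

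Because allocation is by predictable alternation, prefer explicit conditioning on T1 to constraining the T1 group means equal: it also covers imbalance that arises through the screening score. It does not remove bias from unmeasured selection, and the text should say so.

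The cost is one model term and one degree of freedom per analysis. No new data are needed, since T1 FST is the entry measure.
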